### Eligibility criteria

Three different age groups will be included: Group 1 = term infants (37^+0^ to 40^+6^ weeks); Group 2 = preterm infants with postmenstrual ages 28^+0^ to 36^+6^ weeks, and Group 3 = extremely preterm infants with postmenstrual ages 23^+0^ to 27^+6^ weeks. Groups were designed by neonatologist to reflect a variety of common clinical situations encountered in the NICU. Each age group will consist of a variety of subgroups based on different clinical criteria for inclusion (Table 1). Infants with congenital anomalies and surgical conditions (gastroschisis, omphalocele, congenital diaphragmatic hernia), congenital heart disorders, will be excluded to reduce interference of research with care, and reduce interruptions in data collection. Additionally, infants congenital skin infections or known conditions with fragile skin (such as *epidermolysis bullosa*) will be excluded to prevent additional discomfort or complications associated with adhesives. See Fig. 1 for enrollment plan.

**Table 1 table-1:** Study population characteristics.

Groups	Clinical characteristics	Phase 1 (*n* = 24)	Phase 2 (*n* = 24)
Group 1—Term infants with postmenstrual ages at enrollment of 37–42 weeks’	***A:*** healthy* infants in room air at enrollment (*N* = 6)	3	3
	***B:*** infants with perinatal asphyxia undergoing therapeutic hypothermia at enrollment (*N* = 6)	3	3
Group 2—Preterm infants with postmenstrual ages at enrollment of 28^+0^ to 36^+6^ weeks	***C:*** healthy* infants in room air at enrollment (*N* = 6)	3	3
	***D:*** infants on continuous positive airway pressure at enrollment (*N* = 6)	3	3
Group 3—Preterm infants with postmenstrual ages at enrollment of 23^+0^ to 27^+6^ weeks	***E:*** infants on conventional mechanical ventilation at enrollment (*N* = 6)	3	3
	***F:*** infants on high frequency ventilation at enrollment (*N* = 6)	3	3
	***G***: infants on nasal intermittent positive end expiratory pressure at enrollment (*N* = 6)	3	3
	***H***: infants on continuous positive airway pressure at enrollment (*N* = 6)	3	3
**Total:**		24	24

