#### Objective 3. Evaluate the accuracy and coverage of the proposed wireless technology as compared to standard monitoring technology in the NICU

Accuracy will be assessed by comparing both the contents and the quality of the data obtained by the ANNE^®^ sensors and the standard monitoring technology.

In terms of the contents, the recorded data of the raw heart rate (HR), temperature, oxygen saturation (SpO_2_), and respiratory rate (RR) obtained by the ANNE^®^ sensors will be compared to the raw signals obtained by the standard monitoring system. A detailed list of the statistics that will be obtained from the data for comparison can be found in Table 3.

**Table 3 table-3:** List of desired test statistics derived from raw monitor signals.

Heart rate	Average heart rate per epoch (*via* histogram); number of bradycardias and tachycardia per hour; average and maximal duration of bradycardias (<100 beats/min) and tachycardia (>160) per recording (8-h epoch in phase I, 24-h epoch in phase II); number of bradycardias and tachycardia >10 s per hour or per epoch; average heart rate per epoch (*via* tachogram).
ECG (time domain metrics)	minimum, maximum, and median NN interval (*i.e*., the interval between successive R-waves); standard deviation of the NN intervals (SDNN); the standard deviation of the averages of NN intervals in all 5-min segments of the recording (SDANN); the mean of the standard deviations of all NN intervals for all 5-min segments of the recording (SDNNi); the percentage of adjacent NN intervals differing by >50 ms (pNN50); root mean square of successive differences of NN intervals (RMSSD); total number of all NN intervals divided by the height of the 32-bin histogram of all NN intervals (triangular index; HRVTi); and the baseline width of the minimum square difference triangular interpolation of the highest peak of the 32-bin histogram of all NN intervals (TINN).
ECG (frequency domain metrics)	TP: total power (<0.4 Hz), VLF: very low frequency (<0.04 Hz), LF: low frequency (0.04–0.15 Hz), HF: high frequency (>0.15 to <0.4 Hz), and LF/HF ratio using the Welch periodogram
Oxygen saturation	Average, median and interquartile range of SpO_2_ and percentiles (5^th^ and 95^th^); percentage time with values in 5% groupings between 70% and 100%; percentage times spent with SpO_2_ below 80% and above 95%; values in 5% groupings between 70% and 100%

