Respiratory rate	Average value (*via* histogram), number of bradypnea (<40 breaths/min) and tachypnea (>60 breaths/min) per hour; average and maximal duration of bradypnea and tachypnea per recording (8-h epoch in phase I, 24-h epoch in phase II); number of bradypnea and tachypnea >10 s per hour or per epoch; standard deviation, correlation, …tachypnea (above 60), bradypnea (below 40)
Temperature	Average temperature; measurements of temperature variability (using standard deviation of the daily average temperature); percentage times spent in hypothermia (temperature <36.0 °C) and hyperthermia (temperature > 37.5 °C)

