Compare the raw signals from ANNE^®^ and Phillips directly—a preliminary step requires that the signals from ANNE^®^ be resampled to produce segments with an equal number of data points as the Philips monitor (this will be completed as part of the pre-processing in the second class of analysis). Any recording period with under 2 h of usable paired data from the ANNE^®^ and the Phillips will be excluded from comparative analysis. Once equal data samples have been obtained from all usable recordings, the cross-correlation will be used to quantify the latency between matching signals. Performing this operation on segmented epochs throughout a recording will also allow us to determine whether the delay varies with monitoring time or remains constant. The length of epoch segments will be determined based on preliminary analysis. In the time domain, the (PDF) will be used to compare the amplitude structures of signals, while system identification *via* linear models will be used to study the relationship between ANNE^®^ and the Philips monitor. In the frequency domain, the power spectrum will be derived to compare the frequency contents of each signal and extract statistics for the third class of techniques. Lastly, statistical methods, such as the Bland-Altman method, paired *t*-tests, and correlation coefficients, will be implemented to evaluate the agreement between paired measurements or samples.

Compare summary statistics—from the raw signals, summary statistics will be derived and compared to further validate the reliability of ANNE^®^. A detailed list of statistics, both in the time domain and frequency domain, for the various vital signals are outlined in Table 3 alongside traditional measures such as the average heart rate over a specified period, the average respiratory rate over a specified period, and the number of heart beats or breaths detected and/or missed by each device. Graphical representations of desired statistics used for analysis are shown in Fig. 5. The same statistical procedures previously mentioned will be applied once more, this time comparing paired statistics as opposed to matching sample points.

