**Figure 5 fig-5:**
[figure not shown]
Sample of derived comparative statistics for heart rate (HR). (A) Detrended (*via* removing the mean) tachogram representing overlayed heart rate values obtained from Phillips (blue) and ANNE (red) over 4,000 s window (B) probability density function/histogram representing ratio of sample points from each device corresponding to heart rate value computed from tachogram for each respective device over 4,000 s window, Phillips (blue) and ANNE (red) (C) power spectrum representing frequency distribution of the tachogram signals over 4,000 s window for each device Phillips (blue) and ANNE (red).

The above methods have become widely accepted means for evaluating monitor performance in the medical industry and have set a standard for assessing novel devices before deployment. Using MATLAB, we can expect the analysis to be both expressive and efficient, yielding abundant metrics to characterize the reliability and accuracy of ANNE^®^.

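### Table 3's total power, HF and LF/HF stop at 0.4 Hz (24 cycles/min), below the protocol's own 40 to 60 breaths/min, so agreement on them says nothing about heart-rate variability at breathing frequency

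*Protocol article*

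**What the plan says.** Protocol article, Outcomes, Objective 3, Table 3, row on ECG frequency-domain metrics: the bands are "TP: total power (<0.4 Hz), VLF: very low frequency (<0.04 Hz"), then LF, then "HF: high frequency (>0.15 to <0.4 Hz), and LF/HF ratio using the Welch periodogram". No listed band goes above 0.4 Hz, and total power has the same ceiling as HF.

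The respiratory row of Table 3 lists "number of bradypnea (<40 breaths/min) and tachypnea (>60 breaths/min) per hour". The heart-rate row uses "average and maximal duration of bradycardias (<100 beats/min) and tachycardia (>160) per recording".

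The study enrols neonates only. Under Eligibility criteria they range from term infants down to "Group 3 = extremely preterm infants with postmenstrual ages 23^+0^ to 27^+6^ weeks".

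Statistical methods, Objective 3, says that the statistics in Table 3 will be derived for each device and compared as pairs. The paragraph on direct comparison of raw signals adds, with no upper frequency given: "In the frequency domain, the power spectrum will be derived to compare the frequency contents of each signal". The caption of Fig. 5, panel C, describes a "power spectrum representing frequency distribution of the tachogram signals over 4,000 s window for each device".

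**The concern.** The HF band is the highest-frequency band listed and total power is meant to cover the whole spectrum. Both end well below the breathing rates that the same table treats as neither slow nor fast. Variability tied to breathing at those rates falls outside every band. Good agreement on these metrics could then be read as evidence about a part of the spectrum that they never measured.

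The limit is also relevant to device agreement itself. Both devices use the same bands, but that does not make the choice neutral. Some kinds of beat-detection error put most of their power above 0.4 Hz, and the band metrics would register little of it.

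**Working it through.** The protocol gives no derivation of the 0.4 Hz limit, so there is no figure of its own to reproduce.

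**Inputs from Table 3.** Upper limit of HF and total power: 0.4 Hz. Respiratory limits: 40 and 60 breaths/min. Heart-rate limits: 100 and 160 beats/min.

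**Step 1: common units.**
- 0.4 Hz × 60 = 24 cycles/min.
- 40/60 = 0.67 Hz and 60/60 = 1.0 Hz.
- 0.667/0.4 = 1.67, so the bottom of the respiratory range is 1.67 times the cut-off. An infant would have to breathe at under 24/min, far inside the protocol's own bradypnea range, for breathing frequency to fall within HF or total power.

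**Step 2: what the beat series can resolve.** An NN series has one value per beat, so its highest observable frequency is half the heart rate, HR/120 in Hz. This gives 0.83 Hz at 100, 1.0 Hz at 120, 1.25 Hz at 150 and 1.33 Hz at 160 beats/min. At 150 beats/min, (1.25 − 0.4)/1.25 = 68% of the observable range is unused.

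**Step 3: timing error outside the bands, under an assumption.** Assume that R-peak timing errors are independent between beats. Each NN interval then carries the difference of two errors, whose spectrum is proportional to 1 − cos(2πfT), with T = 60/HR seconds. The share of error power below fc is F = 2·T·fc − sin(2π·fc·T)/π. With fc = 0.4 Hz:

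| HR (beats/min) | T (s) | F | Share above 0.4 Hz |
|---|---|---|---|
| 100 | 0.600 | 0.4800 − 0.3177 = 0.1623 | 83.8% |
| 120 | 0.500 | 0.4000 − 0.3027 = 0.0973 | 90.3% |
| 150 | 0.400 | 0.3200 − 0.2688 = 0.0512 | 94.9% |
| 160 | 0.375 | 0.3000 − 0.2575 = 0.0425 | 95.8% |

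A Welch simulation on the beat series gave 84.0, 90.6, 94.8 and 95.8%. After linear resampling at 4 Hz it gave about 74% at 100 and 92% at 160 beats/min.

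**Step 4: other error types.** Shares above 0.4 Hz at 100 to 160 beats/min, on the beat series:
- Independent interval errors, 1 − 2·T·fc: 52 to 70%.
- Timing error correlated over 1 s: 66 to 81%. Over 5 s: 55 to 73%.
- Isolated missed beats: 52 to 70%.
- Ten-beat runs of distorted intervals: about 4 to 6%.

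**Step 5: would a fixed 1.0 Hz limit do?** Below 120 beats/min it exceeds the observable limit from Step 2. Above 120 beats/min the same formula with fc = 1.0 Hz leaves 28% of independent timing-error power outside at 140, 39% at 150 and 48% at 160 beats/min. A limit of 1.0 Hz therefore covers the respiratory range where it can be resolved, but does not capture all timing error.

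**The case against.** The strongest reply is that these bands are one row of a long list. Several other planned measures respond to beat timing:
- Table 3 also has RMSSD, SDNN and pNN50. Independent timing error of variance s² adds 2s² to the NN variance and 6s² to the square of RMSSD, so RMSSD is especially sensitive to the error that the bands miss.
- Statistical methods, Objective 3, adds counts of beats found or missed by each device, and power spectra with no stated 0.4 Hz limit. Fig. 5C is not shown, so no cut-off can be read into it.

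This stands, and it rules out several stronger readings.

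A reader might infer that about 95% of any beat-timing error goes unseen. That figure needs independent error near 150 beats/min. The documents state no error structure, and they expect corruption by movement, which may come in runs. Runs of distorted beats fall mostly inside the listed bands.

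A reader might also infer that the whole spectral comparison is blind above 0.4 Hz. Only the Table 3 band metrics carry that limit.

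A third inference is that these metrics would agree almost regardless of beat-timing accuracy, making the accuracy conclusion too favourable. Sensitivity depends on in-band error relative to true in-band power, and the documents give neither. No section ties the accuracy conclusion to total power, HF or LF/HF, or sets an acceptance limit for them.

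The reply does not remove the band mismatch. RMSSD and SDNN cannot show at which frequency two devices differ, and an unbanded spectrum does not change what the reported band values cover.

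**Conclusion.** The mismatch is real and rests only on unit conversion of the protocol's own figures: the bands end at 24 cycles/min and the respiratory range starts at 40. For infants breathing at 40 to 60/min, agreement on total power, HF and LF/HF gives no information about respiratory-frequency variability.

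The effect on timing error is conditional. For errors independent from beat to beat, about 84 to 96% of the power lies outside the bands at 100 to 160 beats/min. For the other types tested the share is lower, down to about 4 to 6%. Bias in the overall accuracy conclusion is not shown. The point is limited to one row of Table 3, but the limits are explicitly fixed there and are cheap to supplement.

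**What to change.** In Table 3, add total power and HF with an upper limit at the smaller of 1.0 Hz and half the mean heart rate of the epoch (HR/120 in Hz), and LF/HF computed with that HF. Use one shared limit per epoch for both devices, for example from the reference monitor's heart rate. Otherwise each device's own heart rate could give it a different band and create a difference unrelated to spectral agreement. Keep the values below 0.4 Hz for comparison with other work, and state that they exclude breathing frequencies of 40 to 60/min.

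The cost is a change of wording and an integration limit, with no new data. The downsides are small: a few more metrics, extended HF values that cannot be compared with studies using 0.4 Hz, and breathing faster than half the heart rate still not resolvable (above 50 breaths/min at 100 beats/min).

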**Note:**

SDNN, SD of normal- to- normal (NN) or R-wave- to- R-wave intervals; SDANN, SD of the averages of NN intervals in all 5 min segments of the entire recording; SDNNi, mean of the SDs of all NN intervals; RMSSD, root mean square of the differences between adjacent NN intervals; (f) SDSD, SD of differences between adjacent NN intervals; TINN, baseline width of the minimum square difference triangular interpolation of the highest peak of the histogram of all NN intervals measured.

The quality of the signal will be assessed by quantifying the average noise level for each signal, for both monitoring devices.

Continuity of signal will be assessed by quantifying the frequency and duration of connection loss, corruption of signal due movement artifacts, as well as quantification of portion of usable data from each recording period.

### Participant timeline

The overall planned duration of the study is 24 months. Initiation of enrollment for Phase 1 started in August 2022. Phase 2 enrollment and data collection are planned to start in January 2023. Data analysis and results interpretation will take place while patient enrollment and data collection are still ongoing. Details about data collection timeline are provided in Table 4. The last 6 months will be dedicated to manuscript and thesis writing, preparation of final reports, and dissemination of knowledge. Collaborative meetings will be held throughout the entire study period.

**Table 4 table-4:** Participant timeline.

	Study period				
	Enrollment	Allocation	Post-allocation		Close out
Timepoint	}{}$- {t_1}$	0	}{}${t_1}$		}{}${t_2}$
			Phase 1	Phase 2	
**Enrolment:** Screen NICU for eligibility Approach for informed consent Study ID created					
	X				
	X				
		X			
**Data acquisition** – Phillips Intellivue MX450 Electrocardiogram (ECG) Photoplethysmography (PPG) Oxygen saturation (SpO_2_) Respiration rate (RR) – Hourly axial temperature taken by nurses – ANNE^™^ Monitoring System Electrocardiogram (ECG) Photoplethysmography (PPG) Oxygen Saturation (SpO_2_) Respiration Rate (RR) Chest temperature Limb temperature 3-axis accelerometry – Respitrace – Evaluation of skin at site of device placement. – Hourly completion of data collection forms by research team					
			
			X	X	
			X	X	
			X	X	
			X	X	
			X	X	
				
			X	X	
			X	X	
			X	X	
			X	X	
			X	X	
			X	X	
			X	X	
				X	
			X	X	
			X	X	
**Assessments** Healthcare worker survey Parent/guardian survey					
					X
					X

**Note:**

–t_1_ prior to participation in study, 0—following consent to participate, before data acquisition begins, t_1_—data acquisition (either for 8 h, 96 h), t_2_—End of data acquisition, preceding end of study participation.

### Sample size

A convenience sample size of 48 neonates was determined, 24 infants for each phase. However, after data is collected from the first 10 patients, an interim analysis will be performed to determine the precision of measurements between the Phillips and the ANNE^®^ One sensors for each of the parameters. Following that, a reassessment of the appropriate sample size will be performed based on this analysis.

### Recruitment

NICU personnel will be informed about the research project prior to its initiation and given the opportunity to attend information and trainings sessions to promote collaboration and adherence. Upon study initiation, investigators began to check the NICU for eligible participants (see Fig. 1). Once a potential participant is identified members of the research team approach parents or legal guardians to explain the study and obtain informed consent (see Additional File 3).

### Data collection and management

To standardize device administration, all members of the research team will receive training as to how to place devices and connect to study monitor. All data recorded from the different monitoring devices—ANNE^®^ system and standard devices—will be displayed and logged using the BioDASh system. The organization of the data recording framework is shown in Fig. 4. As previously explained, this system provides for the synchronization and aggregation of all data into a single platform for later offline analysis.

**Figure 4 fig-4:**
[figure not shown]
BioDASh system architecture and components. ECG, electrocardiogram; PPG, photoplethysmography; BLE, bluetooth low energy; RIP, respiratory inductance plethysmography; BioDASH, biosensors data aggregation and synchronization system.

The BioDASh application is designed not to interfere with the patient monitor and will not save any protected health information. The streamed data logged by the application will be stored locally on the study laptop with no modifications, post-processing, or filtering. The study laptop will be kept securely with the research team and results will only be shared with team members. Additionally, the logged data will be uploaded to a password protected Dropbox document management software (Dropbox Inc, San Francisco, CA, USA) to which only members of the research team will have access.

#### Device data collection forms

Two predefined data collection (DCF) forms will be used and are included as Supplemental Material (Additional File 4). The forms will provide specification of device placement, infant body position, concurrent therapeutic treatments, room temperature & humidity (RH32-C2; Omega Engineering, Norwalk, CT, USA), hourly axillary temperature measured by bedside nurse and other details which may be relevant when analyzing the data.

These DCF also include a section for reporting any adverse events such as skin irritation, erosion, or bleeding occurring during participation in the study.

#### Skin photographs

The de-identified photographs taken will be uploaded to the password protected team Dropbox account at the end of the data collection of each patient.

#### Survey data

The anonymous responses to the parent and bedside nurse survey will be transcribed throughout the study into an excel file to which only members of the research team will be granted access to.

### Statistical methods

#### Objective 1: Demonstrate the feasibility of continuous wireless monitoring in term and preterm infants with variable degrees of maturation and acuity in the NICU

The number and frequency of the annotations will be used quantitatively to assess challenges related to use of the sensors. Researchers will also report any challenges encountered with the sensor’s battery life, charge duration, and battery durability.

Additionally, we will assess the mean satisfaction scores from nurses and parents as obtained from the surveys. Through review of limited research related to patient satisfaction with ICU monitoring technology, and discussion with the research team a pre-set minim acceptable threshold of 7 out of 10 was set (Poncette et al., 2020; Poncette et al., 2019). This will be used to evaluate the responses by comparing results obtained to pre-set minimum using one sample Wilcoxon test. We will also assess the number of nurses and parents reporting problems with the sensors and identify potential recurring issues as areas for improvement. Descriptive content analysis will be used to code raw responses into categories regarding positive or negative aspects of user experience with the sensors, and the categories and the frequency with which they appear in the surveys will be reported. This analysis and coding of the responses will be accomplished by a member of the research team and a neonatologist.

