## Materials and Methods

### Study design

This is a single center prospective observational study aimed at determining the safety, feasibility, and accuracy of wireless monitoring in the Neonatal Intensive Care Unit. This study design conforms to recommendations by the Standard Protocol Items: Recommendations for Interventional Trials (SPIRIT) (see Additional File 1).

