### Study setting

This study will be conducted in the NICU at the Montreal Children’s Hospital.

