### Outcomes

#### Objective 1. Demonstrate the feasibility of continuous wireless monitoring in term and preterm infants with variable degrees of maturation and acuity in the NICU

Feasibility will be assessed by reporting challenges associated with sensor placement and removal, and acceptability of the continuous wireless monitoring system by parents and bedside nurses.

Data Annotations: To assess the feasibility of using these wireless sensors the number of times a sensor was readjusted, removed, or replaced will be collected *via* the live annotations added in BioDash by the researchers. Researchers may also add annotations related to difficulties applying and removing the sensors.

Parent and Nurse Survey: The research team will also approach parents and bedside nurses at the end of the 4 days with a short, anonymous survey to obtain perceptions about the wireless wearable devices (Additional File 2). The survey consists of three questions:
Were you satisfied with the wireless sensors placed on your baby during their participation in this project? (Score 0—not satisfied at all to 10—very satisfied)What are things you liked about the wireless sensors?Did you encounter any problems with the wireless sensors? If yes, please specify.

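### The satisfaction test against 7 assumes independent responses, but the protocol neither limits nor records repeat surveys by the same nurse; if nurses repeat, the p-value is too small

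*Protocol article*

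**What the plan says.** The Outcomes section, Objective 1, describes the survey: "The research team will also approach parents and bedside nurses at the end of the 4 days with a short, anonymous survey". Its first question asks for a 0 to 10 satisfaction score about one baby's time in the project. Table 4 (Participant timeline) places the healthcare worker and parent surveys at close-out, which the table note defines as the end of that participant's data acquisition. The survey is therefore tied to the infant and recurs with each infant.

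The setting is a single unit: "This study will be conducted in the NICU at the Montreal Children’s Hospital". The number of survey occasions follows from the sample size: "A convenience sample size of 48 neonates was determined, 24 infants for each phase".

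On storage, the Survey data section says: "The anonymous responses to the parent and bedside nurse survey will be transcribed throughout the study into an excel file".

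On analysis, the Statistical methods section, Objective 1, states that "a pre-set minim acceptable threshold of 7 out of 10 was set", and then: "This will be used to evaluate the responses by comparing results obtained to pre-set minimum using one sample Wilcoxon test". It also plans to report how many nurses and parents had problems with the sensors. The text does not mention repeat respondents, a respondent code, the number of surveys expected, the significance level or the sidedness of the test. It does not say whether nurse and parent scores are tested together or apart.

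**The concern.** A one-sample Wilcoxon test treats every score as a separate, independent observation. A nurse who cares for several study infants can be approached several times, and her scores will tend to resemble each other. The sample then holds fewer independent opinions than forms, the standard error is understated, and the p-value against 7 is too small. A few nurses with firm views could move the result in either direction.

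The 7 out of 10 comparison is the only feasibility measure in the Statistical methods section that has both a threshold and a hypothesis test; the others are counts and content coding. The count of nurses reporting problems has the same weakness whatever the p-value, because one nurse who reports the same problem for three infants would be counted three times.

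This is more than an analysis detail. A later analysis plan can specify a clustered test or one value per nurse, but it can apply neither to forms on which a repeat cannot be recognised.

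**Working it through.** The plan gives no figure to reproduce: no significance level, power or expected number of surveys is stated for this test.

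**Inputs from the protocol.** One NICU; 48 infants, hence 48 survey occasions; anonymous forms; one-sample Wilcoxon test; null value 7.

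**Assumptions, not in the protocol.** Nominal level 0.05; one nurse survey per infant (48 in total); m surveys per nurse; within-nurse correlation ρ of 0.3 to 0.7; scores symmetric around 7 under the null.

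**Step 1: how likely are repeats?** If 48 surveys fall at random on a pool of N nurses, the chance that none repeats is N! / [(N − 48)! × N^48].
- N = 80: about 1.2 × 10⁻⁸, or 1 in 80 million.
- N = 200: about 0.2%.

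Without a rule of one survey per nurse, some repetition is close to certain for pools of this size.

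**Step 2: effect on the error rate.** The design effect is DE = 1 + (m − 1)ρ. The actual two-sided error is 2 × [1 − Φ(1.96/√DE)], and the information in 48 surveys equals that of 48/DE independent ones.

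| m | ρ | DE | 1.96/√DE | Two-sided error | Effective n |
|---|---|---|---|---|---|
| 1 | any | 1.0 | 1.96 | 5.0% | 48.0 |
| 2 | 0.3 | 1.3 | 1.72 | 8.6% | 36.9 |
| 2 | 0.5 | 1.5 | 1.60 | 11.0% | 32.0 |
| 2 | 0.7 | 1.7 | 1.50 | 13.3% | 28.2 |
| 3 | 0.3 | 1.6 | 1.55 | 12.1% | 30.0 |
| 3 | 0.5 | 2.0 | 1.39 | 16.6% | 24.0 |
| 3 | 0.7 | 2.4 | 1.27 | 20.6% | 20.0 |

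**Step 3: check by simulation.** The signed-rank test itself was simulated 4,000 times per setting, with continuous and with rounded scores and 48 surveys. The two-sided error was 4.5-4.8% at m = 1, 7.6-13.8% at m = 2 and 11.5-20.3% at m = 3, over ρ of 0.3 to 0.7. With 96 surveys the results are almost the same. This agrees with the formula.

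**Step 4: unequal numbers per nurse.** With random allocation the average design effect is about 1 + (47/N)ρ. At ρ = 0.5:
- N = 40: 1 + 1.175 × 0.5 = 1.59, giving about 12%.
- N = 80: 1 + 0.5875 × 0.5 = 1.29, giving about 8.5%.

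**Step 5: one-sided version.** If the test is one-sided at 5%, 1 − Φ(1.645/√DE) gives about 7.5-10.4% at m = 2 and 9.7-14.4% at m = 3.

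**The case against.** The strongest reply is that the protocol never says a nurse is surveyed twice. It plans to count nurses and parents who report problems, which reads as a count of people and fits one response per person. The survey form is a supplement that is not shown, and an anonymous form can still carry an unlinked code. Handling of repeat respondents is often left to an analysis plan. No go/no-go decision depends on this p-value. Feasibility is also judged from sensor readjustments, removals and replacements, battery problems and free-text answers, in a study that calls its own sample one of convenience.

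Much of this stands, and it limits the point. A reader might infer that the error rate is inflated as a matter of fact and can never be corrected. The documents do not support that: repetition is an inference, and the absence of a code is unknown. A reader might also attach one large inflation figure to the study. The nurse pool, the surveys per nurse and the correlation are all absent from the protocol, so only conditional figures can be given, and they must include the case of no inflation. Nor is there support for extending the argument to parents or to clustering by infant. Parents would mostly answer once, and nothing calculated here covers those sources of correlation.

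What does not stand is leaving the matter wholly to an analysis plan. The survey is scheduled per infant, so repeats are the natural result unless a rule prevents them, and recognising them has to be arranged when the forms are filled in.

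**Conclusion.** The point holds in conditional form. The protocol schedules an anonymous nurse survey for each of 48 infants in one NICU and names a test that needs independent responses, while its text neither limits nor records repeats. If nurses repeat, which is very likely, a nominal two-sided 5% test has an actual error of about 8-13% at two surveys per nurse and 12-20% at three. These figures assume a within-nurse correlation of 0.3 to 0.7. With one response per nurse, or with no correlation, there is no inflation. The number of nurses reporting problems would likewise count forms and not people. Whether this can be corrected at analysis depends on whether the unseen form already carries a code.

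The consequence is confined mainly to the nurse survey within the feasibility objective. It is a cheap improvement worth making and does not threaten the study's main conclusions.

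**What to change.** For the surveys still to be collected:
- If the nurse form does not already carry a code, add either a tick-box for having already completed the survey for another infant, or a self-chosen code not linked to identity. Leave the infant's study ID off the forms, since it would let the team link an answer to a family and end parental anonymity.
- Test nurse and parent scores separately against 7.
- Use one response per nurse in the test: the first response, or the nurse's mean if a code is used. The tick-box identifies first responses only, so it cannot supply a mean. In the simulation, one response per nurse brought the two-sided error back to 4.5-5.0%.
- Count nurses reporting problems on the same one-per-nurse basis.
- Report repeat responses, and any uncoded forms already collected, descriptively.

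The cost is one field on the form, a sentence of analysis wording and a small amendment to the Research Ethics Board. The number of independent nurse responses will fall. Phase 1 enrolment began in August 2022, so uncoded forms already returned cannot be recoded.
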